### Interim analyses

Patient recruitment status will be reviewed every 4 months in planned investigator meetings in which interim analyses will be carried out. If the accrual rate is slower than expected, the principal investigator and co-investigators will discuss the possible reasons and ways to improve the recruitment rate. The interim analyses will not be affected by the results. A data-monitoring group will consist of two independent, external experts who will be responsible for monitoring the progress of the study. If there are significantly more serious adverse events associated with either group after 1 year of commencement of the study, the trial will be terminated as decided by the principal investigator and the data-monitoring group. The same will be applied to the situation where the difference in tumour recurrence between groups is significantly less than expected. The final analysis of the trial will be carried out on an intention-to-treat basis.

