#### Secondary outcomes

These include 30-day, 90-day, and in-hospital mortality, postoperative complications, quality of life, time to functional recovery, 2-year overall survival, 5-year overall survival, and recurrence-free survival. Surgical stress-related cytokines serum interleukin 6 (IL-6) and immunosuppressive acidic protein (IAP) will be measured before surgery and on postoperative days 1 and 7. Measurement of IL-6 and IAP levels will be performed by immunoassay using commercially available kits (MILLIPLEX^®^ MAP Human Cytokine/Chemokine Magnetic Bead Panel, Merck Ltd, Rahway, NJ, USA).

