### Participant timeline

Data accrual will be performed prospectively using wed-based electronic case-report forms (eCRFs) according to the protocol plan (*Table 1* and *Fig. 1*).

**Table 1 zrac166-T1:** Schedule of enrolment, interventions, and assessments of patients

	Study period					
	Enrolment	Allocation	Post-intervention			Close-out
**Time points**	− 1 month	0	Day 1, 3, 7, Day of discharge	Post-discharge 3, 6, 9, 12, 15, 18, 21, 24 months	Post-discharge 30, 36, 42, 48, 54, 60 months, unscheduled visits	Post-discharge 60 months

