**Assessments**						
Clinical evaluation including blood tests	X		X	X		
Radiological evaluation	X			X	X	
Postoperative evaluation including mortality and morbidity			X			
Serum *α*-fetoprotein					X	X
Tumour recurrence evaluation					X	X
QoL assessment					X	X
Patient survival evaluation					X	X
Study closure form						X

QoL, quality of life; LMH, laparoscopic major hepatectomy; OMH, open major hepatectomy.

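### The only stated safety termination rule starts at one year, so it cannot trigger in year 1, although perioperative harms are known within weeks

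*Protocol article*

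**What the plan says.** All the stopping provisions stand in the protocol's Interim analyses section.

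- **Safety rule:** "If there are significantly more serious adverse events associated with either group after 1 year of commencement of the study, the trial will be terminated". The decision lies with the principal investigator and the data-monitoring group.
- **Recurrence rule, tied to the safety rule:** "The same will be applied to the situation where the difference in tumour recurrence between groups is significantly less than expected".
- **Meetings:** "Patient recruitment status will be reviewed every 4 months in planned investigator meetings in which interim analyses will be carried out". The one action attached to them concerns recruitment: "If the accrual rate is slower than expected, the principal investigator and co-investigators will discuss the possible reasons".
- **External group:** "two independent, external experts who will be responsible for monitoring the progress of the study".

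Elsewhere, the Statistical plan provides for continuous data monitoring by the investigators with biostatistical help, and the Blinding section makes the trial fully open. Under Secondary outcomes the early harms are listed: "These include 30-day, 90-day, and in-hospital mortality, postoperative complications". Table 1 has a row "Postoperative evaluation including mortality and morbidity", marked in the column headed "Day 1, 3, 7, Day of discharge".

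**The concern.** The one-year start is a stated timing, not a detail left to another document. It may mean a single comparison at one year, or a rule in force from one year on. Under either reading the rule cannot trigger earlier.

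For recurrence a delay is natural, because recurrence needs follow-up. For harm it is not. The Introduction describes the risks of open major hepatectomy as morbidity of about 30% and hospital mortality below 5%, and the schedule collects these events by discharge. The safety rule therefore waits a year for information that exists within weeks of each operation.

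At stake is the protection of patients enrolled in year 1 if one arm proves clearly more harmful. In this text, no provision for that year names a comparison of safety by arm or a pause as its action. No estimate or test of the primary outcome is affected.

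**Working it through.** **1. How many patients does year 1 hold?**

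Inputs: 330 patients allocated 1:1 (Randomization); recruitment from December 2021 to November 2024, about 36 months (Trial status). The protocol gives no year-1 count and no accrual curve, so the shape is an assumption.

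- Uniform accrual: 330 / 36 = 9.17 per month, so 330 × 12/36 = 110 by month 12.
- Linear ramp over r months, then constant: the final rate is R = 330 / (36 − r/2). The cumulative number at month t is R·t²/(2r) up to month r, and R·(t − r/2) after it.

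| Ramp r (months) | Month 4 | Month 8 | Month 12 |
|---|---|---|---|
| 0 (uniform) | 36.7 | 73.3 | 110.0 |
| 6 | 13.3 | 50.0 | 90.0 |
| 12 | 7.3 | 29.3 | 66.0 |
| 18 | 5.4 | 21.7 | 48.9 |
| 24 | 4.6 | 18.3 | 41.2 |
| 36 | 4.1 | 16.3 | 36.7 |

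Year 1 thus holds about 37 to 110 patients, or 11% to 33% of 330.

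**2. What could reviews at months 4 and 8 show?**

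Method: exact binomial probability that a two-sided Fisher test between arms gives p < 0.05 at month 4, or first at month 8. The test only measures how much information there is; it is not a proposed rule. Under uniform accrual there are about 18 and 37 patients per arm. The protocol gives no serious-adverse-event rate, so all rates are assumptions. The 10% and 30% are its overall morbidity figures for laparoscopic surgery (Discussion) and open surgery (Introduction).

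| True rates | Month 4 | First at month 8 | Total before month 12 |
|---|---|---|---|
| 10% v 30% | 0.205 | 0.309 | 0.513 |
| 20% v 40% | 0.159 | 0.250 | 0.410 |
| 30% v 50% | 0.159 | 0.201 | 0.360 |
| 30% v 40% | 0.052 | 0.070 | 0.122 |
| 3% v 9% (deaths) | 0.011 | 0.036 | 0.047 |

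(Totals are rounded from unrounded parts.)

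- Equal arms at 10, 20, 30 and 40%: false-flag probability 0.021, 0.041, 0.044 and 0.046.
- One-month outcome lag: 9.17 × 3 = 27.5 and 9.17 × 7 = 64.2 patients have outcomes, about 14 and 32 per arm. For 10% v 30% the total falls from 0.51 to 0.43.
- Slower accrual, 10% v 30%, no lag: 0.31, 0.15, 0.08 and 0.03 for ramps of 6, 12, 18 and 36 months.

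**3. What if the significance rule itself were moved earlier?**

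An unadjusted chi-squared test at p < 0.05, repeated at months 4, 8 and 12 (18, 37 and 55 per arm) with equal arms at 10, 20, 30 and 40%, gives a cumulative false-positive rate of 0.102, 0.107, 0.109 and 0.114. One test at month 12 gives 0.050 or 0.051. Early reviews should therefore prompt judgement, not an automatic stop.

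**4. How much exposure could be avoided?**

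For 10% v 30% under uniform accrual, if every flag halted enrolment: 0.205 × (110 − 37) + 0.309 × (110 − 73) = 15.0 + 11.4, about 26 patients. About 13 of them would be in the worse arm, and 13 × 0.20 = 2.6 excess events. With a 12-month ramp the result is about 6 patients and 0.6 events.

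**The case against.** The strongest reply has four parts.

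*Year 1 is already overseen.* There are 4-monthly interim analyses, two external experts, continuous monitoring and open-label data. A condensed article may leave the content of the interim analyses and the group's remit to a fuller document. This stands as a limit. A reader might infer that nobody watches safety in year 1, or that the trial cannot be paused then; the protocol supports neither. Events from year 1 also still count in the later comparison. What remains is that the one safety rule this text does date is dated at a year.

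*A minimum information time is sensible for a significance rule.* This stands too: repeated unadjusted looks roughly double the false-positive rate. It argues for keeping the one-year start for that kind of rule, but not against an earlier review based on judgement.

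*The 10% v 30% case is not an unexpected harm.* It is the protocol's own morbidity contrast, with the standard open arm worse, and it is overall morbidity, not serious adverse events. If those rates carried over, an early flag could simply show the expected perioperative benefit of laparoscopy, and a pause would put the 2-year recurrence-free survival question at risk. This is a real cost, and the remedy has to allow for it.

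*The gain is small.* Only 20-point gaps are reasonably visible early, mortality differences hardly at all, and slow accrual removes most of the benefit. This is correct and sets the weight of the point. Low power against moderate differences is still no reason to wait on a very large one.

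**Conclusion.** The point holds as a cheap improvement. The only stated safety termination rule cannot trigger in year 1, when about 37 to 110 of 330 patients would be enrolled. The figure of 110 is the top of that range and needs uniform accrual over 36 months. It counts patients enrolled, not harm that could have been avoided. The timing fits recurrence and does not fit perioperative harm.

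The benefit of an earlier review is confined to very large imbalances and shrinks with slower accrual or delayed outcomes. The detection figures rest on assumed event rates and, apart from the lag check, on outcomes being known for everyone enrolled at each look. The finding about the rule's timing rests on the wording alone and needs none of these assumptions. Nothing here bears on the validity of the primary analysis.

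**What to change.** In Interim analyses, keep the one-year start for the recurrence rule and for any termination based on a significance test, and add text such as:

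> At each 4-monthly review, from the first, the data-monitoring group will examine serious adverse events and in-hospital and 30-day deaths by arm. It may recommend a pause or termination at any time on its own judgement, weighing the direction of any difference and the 2-year recurrence-free survival question. An unadjusted p < 0.05 will not by itself stop the trial.

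No numerical mortality trigger is needed, and the final decision stays with the principal investigator and the group.

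The cost is two or three sentences and a little more reporting, using the existing group, schedule and data. There are three downsides:

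- Early reviews will be uninformative about moderate differences and most mortality differences.
- With equal arms there is a 2–5% chance of a false flag by month 8, if the group looked at Fisher p < 0.05 under uniform accrual.
- A flag may reflect the lower morbidity expected of laparoscopic surgery, which is why the text asks the group to weigh direction before recommending a pause.

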### Ethics

An information sheet will be provided, and each subject will be given the opportunity to seek medical advice or to discuss the study with friends or family prior to involvement. Written informed consent will be mandatory for inclusion and patients will be free to withdraw it at any time. This study will be performed in accordance with the ethical standards of the Declaration of Helsinki of 1975 and its later versions. Ethics approval from the institutional review broad of each centre will be obtained.

### Dissemination plan

The protocol of this trial has been registered in Clinicaltrials.gov. The final report on primary and secondary outcomes will be published upon the completion of 5-year follow-up. Both interim analysis and final analysis will be presented at local and international conferences.

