### Statistical plan

The 2-year recurrence-free survival (primary outcome) and overall survival will be evaluated by Kaplan–Meier method and compared by the log rank test. Other secondary outcomes will be compared using the chi-squared test or Fisher’s exact test for categorical variables, and the Mann–Whitney *U* test for continuous variables. *P* < 0.050 will be considered statistically significant. Statistical analysis will be performed using SPSS version 11.0 (SPSS Inc., Chicago, IL, USA).

All clinical data including patients’ demographics, operative details, tumour characteristics, and clinical outcome measure will be collected and centralized at the principal investigator’s centre using a password-protected web-based system to ensure confidentiality of personal information. Continuous clinical data monitoring will be performed by the principal investigator and co-investigators with the help of biostatisticians and research assistants. The data set will be kept confidential until the publication of trial results.

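### Interim analyses run in investigator meetings, with the principal investigator co-deciding on differences between arms and a conference presentation planned, may release results by arm before the 2-year endpoint is mature

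*Protocol article*

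**What the plan says.** All references are to the protocol article.

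- **Interim analyses, forum:** "Patient recruitment status will be reviewed every 4 months in planned investigator meetings in which interim analyses will be carried out".
- **Interim analyses, triggers:** two comparisons between arms can end the trial. One is on safety: "If there are significantly more serious adverse events associated with either group after 1 year of commencement of the study". The other is on recurrence: "the situation where the difference in tumour recurrence between groups is significantly less than expected".
- **Interim analyses, decision:** on the safety trigger, "the trial will be terminated as decided by the principal investigator and the data-monitoring group", and the same applies to the recurrence trigger.
- **Interim analyses, independent monitors:** "A data-monitoring group will consist of two independent, external experts who will be responsible for monitoring the progress of the study". Sole access to comparative data is not mentioned.
- **Statistical plan:** "Continuous clinical data monitoring will be performed by the principal investigator and co-investigators", helped by biostatisticians and research assistants.
- **Dissemination plan:** "Both interim analysis and final analysis will be presented at local and international conferences". The final report follows completion of 5-year follow-up.
- **Blinding:** none, for patients, investigators, surgeons or supporting staff.
- **Trial status:** recruitment from December 2021 to an anticipated close in November 2024.

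**The concern.** Read together, these rules open three routes by which results by arm can leave the independent monitors: the investigator meeting, the principal investigator's share in the termination decision, and the conference presentation. Recurrence drives the primary outcome, so the second trigger is in effect an interim look at the primary comparison.

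The trial is open-label, so masking cannot protect the conduct of the trial or the detection of recurrence. Restricting knowledge of the aggregate difference is the main protection left. Staff who know that difference could act on it, without intending to, at three points that the protocol leaves to judgement after allocation:

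- withdrawal once the envelope is opened, 1 day before surgery;
- exclusion at surgery, including the surgeon's decision to abort before resection (Eligibility criteria);
- recurrence work-up, because Follow-up allows visits every 3 to 6 months and Table 1 allows unscheduled ones.

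The first two matter to the extent that those patients leave the analysis. The third can shift recorded recurrence times differently in the two arms. None of these can be reliably undone at the analysis stage. A second cost is that an early estimate made public may rest on very few events.

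**Working it through.** The plan gives no figure for its interim looks, so there is none to reproduce. The check has two parts.

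**1. Timing, from the document's dates**

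- Recruitment December 2021 to November 2024 = 36 months. At one meeting every 4 months: 36/4 = 9 meetings during recruitment.
- The safety trigger applies after 1 year, about December 2022. With even accrual, 330 × 24/36 = 220 patients would still be unrandomised.
- The last patient reaches 24 months about November 2026 and 5 years about November 2029.
- An interim analysis, as distinct from the final one, therefore falls within follow-up. Whether it is presented before or after November 2026 is not stated.

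**2. How much information an early look holds**

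Inputs: 165 per arm (Sample size); 2-year recurrence-free survival of 72% open and 88% laparoscopic (Sample size). The section's second scenario, 2-year recurrence of 50% v 30%, is treated here as recurrence-free survival of 50% v 70%. Assumptions: uniform accrual over 36 months, exponential recurrence-free survival, no dropout.

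Hazard per month: λ = −ln(S)/24. This gives 0.01369 for 72% and 0.00533 for 88%.

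Expected events per arm by month t (t ≤ 36): (165/36) × [t − (1 − e^(−λt))/λ].

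| Month | Randomised | Events, 72% v 88% | Events, 50% v 70% |
|---|---|---|---|
| 12 | 110 | 4.3 + 1.7 = 6.0 | 8.5 + 4.6 = 13.1 |
| 24 | 220 | 16.2 + 6.7 = 23.0 | 30.7 + 17.5 = 48.1 |
| 36 | 330 | 34.7 + 14.9 = 49.6 | 62.4 + 37.2 = 99.6 |

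(Sums are taken before rounding.)

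Now suppose there is no true difference, with both arms at the open-surgery rate. SE(log HR) ≈ 2/√events, and the chance that the estimated hazard ratio falls outside 0.67 to 1.5 is 2 × [1 − Φ(ln 1.5/SE)], with ln 1.5 = 0.405.

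| Month | Both arms 72%: events, SE, chance | Both arms 50%: events, SE, chance |
|---|---|---|
| 12 | 8.6, 0.684, 55% | 17.0, 0.485, 40% |
| 24 | 32.5, 0.351, 25% | 61.3, 0.255, 11% |
| 36 | 69.4, 0.240, 9% | 124.8, 0.179, 2% |

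A result released in the first two years could thus look like a sizeable effect in either direction by chance alone. The problem shrinks by the end of recruitment. These figures measure imprecision, not bias in the final result.

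**The case against.** The other side has a fair case, and several parts of it stand.

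- **Undated presentation.** A reader might infer that interim results will be presented while patients are still being randomised. The Dissemination plan gives no date, so this is an inference. The presentation could even be the mature 2-year primary analysis, ahead of the 5-year report. That reading stands as possible, and the fix keeps that release.
- **Confidentiality.** A reader might see a contradiction with the Statistical plan: "The data set will be kept confidential until the publication of trial results". There is none. That sentence, like the Data Availability section, concerns the data set, and presenting summary results does not release it. For the same reason it does not protect interim results.
- **Accrual only.** The sentence on 4-monthly meetings has recruitment as its subject, and the next one deals with slow accrual. This softens the first route. It does not touch the two triggers based on differences between arms, or the presentation commitment. Nor does anything say that the meetings continue after recruitment ends, so counting them to the last patient's 24 months is unsupported.
- **Joint decision without data.** The principal investigator could decide on a recommendation alone, and a monitoring charter may say so. That is compatible with the text, but the text as written makes the principal investigator a co-decider and sets no limit on access.
- **Who is offered the trial.** A change in who is approached before randomisation alters the case mix of both arms. By itself it does not bias the randomised comparison, so it is not part of this point.
- **Open label already.** Surgeons know each patient's arm anyway. Knowing individual allocations is still different from knowing the aggregate difference.

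**Conclusion.** The point holds as a flaw in stated rules. The protocol has interim analyses in investigator meetings, a principal investigator who co-decides on safety and recurrence by arm, and an undated commitment to present the interim analysis. Nothing in it limits results by arm to the two external experts or delays their release until the primary endpoint is mature. In an unblinded trial this exposes the 2-year comparison to a bias that can be avoided.

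The bias is conditional: it arises only if results by arm reach investigators or the public before the last patient has 24 months of follow-up. Its size cannot be derived from the document. What can be sized is the imprecision of an early look: about 6 events at month 12 and 23 at month 24 at 72% v 88% (13 and 48 at 50% v 70%), under even accrual, exponential recurrence-free survival and no dropout. It should be corrected because the safeguard is cheap and the damage could not be repaired afterwards.

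**What to change.** **Interim analyses section.** Limit the 4-monthly investigator meetings to pooled accrual and data quality. State that any comparison by arm is prepared by the trial biostatistician and goes only to the two external experts. State that those experts make the recommendation, and that the principal investigator acts on it without seeing the comparative data.

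**Dissemination plan.** Replace the commitment to present interim analyses with a statement that the first release of any outcome by arm is the primary 2-year analysis, once the last patient has 24 months of follow-up, with 5-year outcomes reported later. If the interim presentation was meant to be that analysis, this wording names it and nothing is lost.

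**Cost.** A wording amendment; the external experts and biostatisticians are already in the plan. The downside is that there are no earlier conference presentations and the principal investigator gives up direct access to comparative interim data.

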## Discussion

The aim of the AP-LAPO trial is to test the hypothesis that LMH is associated with reduced surgical stress and immunosuppression compared with OMH resulting in lower tumour recurrence rates and better survival.

OMH for HCC is associated with major morbidity of up to 40 per cent in high-volume centres^25–28^ as well as a high tumour recurrence rate. The 3-year recurrence rate has been reported to be greater than 50 per cent^7,29^ with most of these recurrences occurring in the liver remnant. Manipulation of the tumour during OMH along with postoperative immunosuppression induced by surgical stress have been suggested as factors that may increase risks of recurrence in the liver remnant^30^.

Recent series have proven the feasibility and safety of LMH for HCC^17^. The conversion and morbidity rates are around 10 per cent. Fewer wound and chest complications and shorter hospital stays are seen after LMH compared with OMH^10^. An animal study has shown that LMH results in less surgical stress and immunosuppression than OMH^9^. Theoretically, laparoscopic instrumentation causes less manipulation of the tumour that might limit cancer-cell dissemination, reducing tumour recurrence and prolonging survival. The reduced immunosuppression might also influence recurrence rates and survival in LMH. This theory is supported by a recent meta-analysis based on reconstructed time-to-event data^11^.

To date, only retrospective studies using propensity score matching have compared LMH and OMH^8,12^. Sample sizes were small (less than 40) in each matched group and the reported 2-year overall and recurrence-free survival were comparable between OMH and LMH. This trial aims to provide high-level evidence to see if there is added value of laparoscopic surgery in the treatment of patients with HCC.

